#### Career consultants

Career consultants provide specialised education and vocational support including career exploration, planning and transition, managing uncertainty and indecision, guidance on education pathways and enrolment, study support, job application processes, career assessments and discussions around disclosure and reasonable adjustments. Career consultants on *Momentum* are experienced and qualified in career development practice and registered with national regulatory bodies. Functional and vocational outcomes, including return to usual career-related activities (eg, work, school, further education), and building vocational skills that can provide purpose, improve self-confidence, self-efficacy and career adaptability. These skills can further improve vocational outcomes and resilience to career shocks which affect ongoing mental health, recovery and relapse prevention.

Career support is available to all young people on *Momentum*. Career consultants work flexibly, responding to individual needs to establish key goals. Support is provided through direct messaging, with phone contact offered depending on needs and preferences. Career consultants consider all potential influences on a young person’s career including the environment and perceived self-efficacy, thus working within the Systems Theory Framework of Career Development^59^ and social cognitive career theory.^60^ The overarching approach ensures consistency with the key theoretical underpinnings of *Momentum,* including SDT and supportive accountability to build engagement, trust and encourage completion of activities.

Career consultants draw on a repertoire of evidence-based career education activities within *Momentum,* aligned to the Australian Blueprint for Career Development,^61^ and direct young people to relevant and reputable external resources where required. All content and engagement aims to build employability skills aligned to the Core Skills for Work Developmental Framework^62^ and guided by career construction theory,^63^ supporting the young person to undertake activities to build their own career self-management skills and career adaptability. A collaborative approach with peer workers and clinicians on *Momentum* and relevant external stakeholders supports each young person to work towards their education and vocational goals.

#### Peer workers

Peer workers are young people who have been trained to intentionally share their lived and living experience of mental ill-health. Peer workers moderate the online ‘Community’ (including TiO) and chat individually with young people on the platform via direct messaging. Peer workers also lead monthly online ‘hangouts’ to reinforce connections and promote engagement. Peer workers are supervised by the peer work coordinator. The peer work model is designed to normalise experiences, counteract stigma and promote platform engagement. Peer workers are thus integral to the provision of social support via *Momentum*—a proposed mechanism of action in the study.^64^

### Persuasive systems design framework

The principles in the Persuasive Systems Design (PSD)^38^ framework are intended to influence users’ behaviours and attitudes, guiding them toward achieving specific goals. These principles are aimed at enhancing user motivation, increasing engagement and promoting long-term behaviour change, making systems both effective and compelling in achieving desired outcomes.

*Momentum* incorporates 14 of the 28 principles outlined in the PSD. Table 2 provides a detailed overview, including the domain, principle, description and an example of how each persuasive principle is applied within the intervention.

**Table 2 T2:** Application of persuasive design principles in the *Momentum* intervention

Principle	Description	Momentum example
Reduction	Reducing complex behaviours into manageable tasks	Therapeutic activities are segmented into bite-sized steps. Clinicians support young people to set manageable goals for platform use.
Tunnelling	Guiding the user through a process or experience in a manageable way	The system guides young people through their therapeutic journey, providing a clear and structured pathway for progression.
Tailoring	Customising information to reflect the needs, interest, personality and usage context of a user group	Customised content and activities align with young people’s developmental stage and specific mental health needs.
Personalisation	Providing individualised content and experiences	Personalised content recommendations that are linked to the young person’s specific goals.
Rehearsal	Providing opportunities to practise a behaviour to help users prepare for real-world situations	Encourages young people to practise behaviours by applying them in real-world scenarios, reinforcing learning through repetition and real-life application.
Praise	Providing praise or positive feedback for using the system	Moderators acknowledge progress and reinforce positive behaviour.
Reminders	Remind users of their target behaviour	Clinicians can send reminders, ensuring timely prompts to encourage engagement and task completion.
Suggestions	Offer relevant suggestions to the user	Clinicians suggest relevant content, offering tailored recommendations that support progress and engagement.
Liking	A visually attractive system	Designed in combination with young people and designers to create user-friendly and visually appealing experience.
Surface credibility	The system conveys a competent appearance	Provides clear and accessible information, such as terms and conditions, contact phone numbers and distress support advice.
Trustworthiness	Information provided should be fair and objective	Ensures content is supported by evidence-based theories and practices.
Expertise	Information provided should demonstrate knowledge, experience and competence	*Momentum’s* content is designed by a team of clinicians, and the moderation team is staffed by psychologists, social workers, peer support workers and career consultants, ensuring expertise and professional oversight in the platform’s delivery.
Normative influence	Facilitate the gathering of users with similar goals, fostering a sense of community and shared norms	The community within *Momentum* fosters a sense of belonging by bringing together young people with similar lived experience. This creates a supportive environment that promotes normalisation and encourages social connections, reinforcing the notion that young people are not alone in their journey.
Social facilitation	Users can perceive that others on the system are performing the target behaviour	*Momentum* supports social facilitation by providing talking points on content, allowing young people to discuss and share their experiences of trying new skills.

### Safety protocol

The safety protocol comprises three levels of security: (1) system and privacy protection; (2) online safety and (3) clinical safety.

The *Momentum* platform is hosted on Amazon Web Services. Amazon Web Services and Orygen Digital meet standards of responsible business practice. Identity management and networking are handled by Orygen Digital’s engineering department according to Orygen (National) Standards, which meet Australian research requirements. In addition, *Momentum* has a wide range of measures to secure the application and database against unauthorised access. These measures conform to industry best practice as defined by the Open Web Application Security Project (www.OWASP.org). Privacy and online safety are managed in accordance with the Australian Communications and Media Authority.

On onboarding, the *Momentum* clinician carries out an initial orientation with *Momentum* participants, including details of the terms of use. Participants are required to accept and comply with the guidelines for safe use of *Momentum*. When needed, participants are offered guidance on appropriate usage of the system. All users are asked to nominate an emergency contact person, such as a close family member. *Momentum* includes a ‘report function’ that enables young people to report a concern about any material posted by a user. Moderators assess each report and respond accordingly, which may include removing material and, in some cases, deactivating or restricting the post author’s account. Participants are also able to hide their profile and activity should they become concerned about their privacy.

Clinical risk is managed through both manual and automated procedures. First, clinical moderators monitor the system twice daily on weekdays and once daily on weekends for evidence of clinical risk or deterioration. Any detected increased risk activates the *Momentum* risk and safety protocol, which includes one or more of the following: a risk assessment with the young person, informing the research team, alerting the emergency contact nominated by the participant and liaising with suitable emergency services where necessary. In addition, the system incorporates visible emergency guidelines and contact information. Finally, *Momentum* includes an automated keyword detection function, which activates each time a participant posts a contribution indicative of clinical risk, or a post containing potentially offensive words. The function blocks posts with notifications sent to the young person and the moderator, who can ‘unblock’ the post should they determine it unproblematic.

If, while in contact with a young person, the clinical moderator becomes aware of a clinically significant deterioration of symptoms, increased risk of suicide or a hospital admission, the clinician performs an assessment to determine the risks and benefits of a temporary withdrawal from *Momentum*. Based on this assessment, and in consultation with the young person, the clinical moderation team determines whether their account is temporarily suspended, or their level of access is restricted. Following suspensions or restrictions to a user’s account, the clinician will contact the young person at monthly intervals to ascertain whether the account is to be reactivated.

### Outcomes

#### Primary outcome and measure

The primary outcome is social functioning over 12 months. Social functioning will be measured by the Global Functioning: Social Scale, a valid and reliable instrument designed to measure social functioning in UHR.^65 66^

#### Secondary outcomes and measures

Secondary outcomes and measures include:

*Depressive* symptoms will be measured by the Quick Inventory of Depressive Symptomatology-Self-Report self-report instrument^67^ at baseline, 4 months, 8 months and 12 months.*Anxiety* will be measured by the Generalized Anxiety Disorder 7-item Scale^68^ at baseline, 4 months, 8 months and 12 months.*Role functioning* will be measured using the Global Functioning: Role Scale.^65^*Vocational and education status* will be self-reported by participants at baseline, 4 months, 8 months and 12 months (including the participant’s report of employment and educational activities in between assessments).*Cost-effectiveness* will be assessed using an adapted self-reported Resource Use Questionnaire (RUQ) to determine the broader resource use of participants (eg, community mental health services, hospitalisations, work and educational impacts, etc) and the Assessment of Quality of Life-Eight Dimension (AQoL-8D) questionnaire, which measures health-related quality of life and can be used to calculate QALYs.^69^

#### Other measured outcomes

Additional exploratory outcomes, potential covariates and intervention-only outcomes are outlined in table 3.

**Table 3 T3:** Schedule of enrolment, assessments and intervention

	Enrolment		Post randomisation		
	-t_1_ - 0	0	t1 (4 months)	t2 (8 months)	t3 (12 months)
Informed consent	✓				
Eligibility screen	✓				
Primary outcome and measure					
Social functioning (Global Functioning: Social)	✓		✓	✓	✓
Secondary outcomes and measures					
Depression (QIDS)	✓		✓	✓	✓
Anxiety (GAD-7)	✓		✓	✓	✓
Social anxiety (LSAS)	✓		✓	✓	✓
Role functioning (Global Functioning: Role)	✓		✓	✓	✓
Vocational status (RUQ)	✓		✓	✓	✓
Cost-effectiveness (RUQ and AQoL-8D)	✓		✓	✓	✓
Exploratory outcomes and measures					
Self-efficacy (SES)	✓		✓	✓	✓
Social support (SPS)	✓		✓	✓	✓
Subjective well-being (SWLS)	✓		✓	✓	✓
Transition to psychosis (Abbreviated CAARMS)	✓		✓	✓	✓
Attenuated psychotic symptoms (Abbreviated CAARMS)	✓		✓	✓	✓
Quality of life (AQoL-8D)	✓		✓	✓	✓
Stress (PSS)	✓		✓	✓	✓
Loneliness (UCLA Loneliness Scale^77^)	✓		✓	✓	✓
Self-esteem (Rosenberg SES)	✓		✓	✓	✓
Psychological well-being (BPNS)	✓		✓	✓	✓
Sleep quality (PSQI)	✓		✓	✓	✓
Suicidal ideation and attempts (CSSRS)	✓		✓	✓	✓
Strengths use (SUS)	✓		✓	✓	✓
Mindfulness skills (FMI)	✓		✓	✓	✓
Self-compassion (SCS-SF)	✓		✓	✓	✓
Substance use (ASSIST)*	✓				✓
Anomalous self-experience (IPASE)*	✓				
History of trauma (ACE)*	✓				
Randomisation		✓			
Intervention		Continuous			
Comparator		Continuous			
Digital phenotype (AWARE-Light^78^)		Continuous			
Daily social functioning and subjective well-being (SEMA3 application)		Daily			
Intervention group-only outcomes and measures					
Intervention acceptability (qualitative evaluation via semistructured interview)					✓
Therapeutic alliance (WAI-C, WAI-T)		✓	✓	✓	✓
Usage data		Continuous			

* Potential covariates.

ACE, Adverse Childhood Experience Questionnaire^79^; AQoL-8D, Assessment of Quality of Life – Eight Dimension^69^; ASSIST, Alcohol, Smoking and Substance Involvement Screening Test^80^; BPNSS, Basic Psychological Needs Satisfaction Scale^81^; BPNSS, Basic Psychological Needs Satisfaction Scale^81^; CAARMS, Comprehensive Assessment of At Risk Mental States^82^; CSSRS, Columbia-Suicide Severity Rating Scale^83^; FMI, Freiburg Mindfulness Inventory^84^; GAD-7, Generalized Anxiety Disorder 7-item scale^68^; IPASE, Inventory of Psychotic-Like Anomalous Self-Experiences^85^; LSAS, Liebowitz Social Anxiety Scale^86^; PSQI, Pittsburg Sleep Quality Index^87^; PSS, Perceived Stress Scale^88^; QIDS-SR, Quick Inventory of Depressive Symptomatology-Self-Report^67^; Rosenberg Self-Esteem Scale, Rosenberg SES^89^; RUQ, Resource Use Questionnaire; SCS-SF, Self-Compassion Scale Short Form^90^; SEMA3, Smartphone Ecological Momentary Assessment^91^; SES, Self-Efficacy Scale^92^; SPS, Social Provisions Scale^93^; SUS, Strengths Use Scale^94^; SWLS, Satisfaction with Life Scale^95^; WAI-T, Working Alliance Inventory client version (WAI-C) and therapist version^96^.

### Data collection methods

Multiple methods will be employed to assess study outcomes. These include blind interviewer ratings, self-report and usage data from the *Momentum* system.

Research assessments will be administered either in person, via phone or telehealth platform. The research assistants (RA) will administer interviewer-rated measures verbally, documenting the responses in a hard or soft copy of the case report form (CRF). Self-report measures are delivered to the participant electronically via Orygen National’s Research Project Management System (RPMS). The initial assessment will take approximately 1.5–2 hours, with follow-up assessments expected to take approximately 1 hour.

Research assistants will be trained in the administration of all interviewer-administered measures. Eligibility for the study will be confirmed after consultation with the study coordinator. Follow-up assessments will be discussed in weekly review meetings.

Several strategies will be embedded to promote participant retention, including a flexible assessment window, accommodating availability of research assistants and honing research assistant interview skills to minimise time commitment at larger assessment points.

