### Participant timeline

Following informed consent, participants are enrolled in the trial and screened for eligibility. Once eligibility is established, participants complete the baseline assessment within a 1 month window. Participants are randomised after the completion of baseline measures. Participants in the intervention group receive access to *Momentum* after randomisation for the duration of the study period. All participants complete follow-up assessments at 4 months, 8 months and 12 months, respectively.

The participant timeline is outlined in table 3.

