### Randomisation: sequence generation, allocation concealment mechanism and implementation

The randomisation schedule is generated by a statistician independent of the study, programmed in the RPMS and not accessible by the study team. Participants are randomly assigned to the treatment condition via the RPMS using randomly permutated blocks with a 1:1 allocation ratio. Participants are stratified by age (<18 years and ≥18 years), sex at birth and recruitment site.

Once eligibility is established, participants complete the baseline assessment, after which participants are randomised by the research assistant via a secure online RPMS. The RPMS sends an automated email to the study coordinator and principal investigator, notifying them of the outcome of randomisation. The study coordinator informs each participant of their treatment allocation via SMS.

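### The study coordinator is consulted on eligibility and also receives every earlier allocation, which under permuted blocks weakens allocation concealment

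*Protocol article*

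**What the plan says.** Under Data collection methods, the protocol article states: "Eligibility for the study will be confirmed after consultation with the study coordinator".

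The section on randomisation gives the same role full knowledge of past allocations: "The RPMS sends an automated email to the study coordinator and principal investigator, notifying them of the outcome of randomisation", and "The study coordinator informs each participant of their treatment allocation via SMS".

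That section also fixes the method. Assignment is made "using randomly permutated blocks with a 1:1 allocation ratio", and "Participants are stratified by age (<18 years and ≥18 years), sex at birth and recruitment site". The stated protection is that a statistician independent of the study generates the schedule, which is "programmed in the RPMS and not accessible by the study team" (RPMS is the trial's Research Project Management System).

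The order of steps is: "Once eligibility is established, participants complete the baseline assessment, after which participants are randomised by the research assistant". Participant timeline adds: "Once eligibility is established, participants complete the baseline assessment within a 1 month window".

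Nothing in the article separates the person who advises on eligibility from the person who receives the allocations.

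**The concern.** Allocation concealment has two parts. The list must be hidden, and those who influence entry must be unable to infer the next assignment. The plan secures the first. The second is weakened, because permuted blocks return each stratum to balance. The arm that is behind in a stratum is therefore more likely to come next, and anyone who knows the past allocations can see which arm that is. Age, sex and site are known at screening, so the relevant stratum can be identified when eligibility is discussed.

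If a view on a borderline candidate leaned with the expected arm, even without intent, the arms would differ in prognosis from the start. Rater masking and the intention-to-treat principle act after entry and do not correct this.

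**Working it through.** **Inputs from the protocol article.** 1:1 permuted blocks; strata of age (2) × sex (2) × site; 220 to be randomised and 180 required for analysis (Sample size); seven services named (Trial design and setting: three in Victoria, four in New South Wales).

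**Assumptions.** Block size is not given, so 2, 4, 6 and mixed 4/6 are tried. If every named service is a stratification level, there are 2 × 2 × 7 = 28 strata, averaging 220/28 = 7.9 participants. With only two site levels there are 8 strata, averaging 27.5.

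**The plan's own figures.** A two-sided two-sample t test with d = 0.45, 85% power and alpha 0.05 gives 180 in total, and 180/0.82 = 219.5, rounded up to 220. Both reproduce. The article states no figure on predictability.

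**Chance of a correct guess.** The rule is to guess the arm with fewer assignments so far in the stratum, and toss a coin when they are level. It needs no knowledge of block size, because completed blocks are balanced. For a stratum of 8:

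- Blocks of 2: the first place is right with probability 1/2, the second always. (0.5 + 1)/2 = 75%.
- Blocks of 4: the four places are right with probabilities 1/2, 2/3, 2/3 and 1. Their sum is 2.833, and 2.833/4 = 71%.
- Blocks of 6: a full block yields 4.1 correct guesses on average. The first two places of the next block add 1/2 + 3/5 = 1.1. (4.1 + 1.1)/8 = 65%.
- Mixed 4/6 (simulated): 67%.

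**Sensitivity to strata** (simulated, blocks of 2, 4, 6 and mixed 4/6):

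| Strata | 2 | 4 | 6 | 4/6 |
|---|---|---|---|---|
| 28, filled at random | 73% | 68% | 65% | 67% |
| 28, equal | 75% | 70% | 65% | 67% |
| 8, equal | 75% | 70% | 67% | 69% |

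The result does not depend on having many small strata.

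**Effect of the gap before randomisation.** Others in the stratum may be randomised after eligibility is discussed but before the candidate is randomised. With an assumed uniform lag of 0 to 1 month and blocks of 4, the rate is about 69% for 8 participants per stratum over 36 months, and about 61% for 27 per stratum over 12 months.

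**Possible bias.** Suppose eligibility advice moves the expected outcome of those enrolled by +δ/2 when one arm is guessed and −δ/2 when the other is. With a correct-guess probability p, the difference between arms is δ(2p − 1). The standard error of a simple difference with 180 analysed is 2/√180 = 0.149 SD. The one-sided error is Φ(−1.96 + bias/0.149). With p from the randomly filled 28 strata:

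| δ (assumed) | p | Bias | One-sided error |
|---|---|---|---|
| 0.05 SD | 0.65 | 0.05 × 0.30 = 0.015 SD | 3.2% |
| 0.05 SD | 0.73 | 0.05 × 0.46 = 0.023 SD | 3.6% |
| 0.2 SD | 0.65 | 0.2 × 0.30 = 0.060 SD | 6.0% |
| 0.2 SD | 0.73 | 0.2 × 0.46 = 0.092 SD | 9.0% |

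The nominal value is 2.5%. The error rates ignore any adjustment for baseline.

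**The case against.** Several points on the other side stand, and they limit the finding.

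- **Influence.** The coordinator is consulted and is not named as the decider. Research assistants, who are to be blind, carry out the interviews and perform the randomisation. In New South Wales a site liaison identifies candidates. The allocation email goes to neither of these roles.
- **Room for judgement.** The acute-risk exclusion is defined in the text and the developmental exclusions require a diagnosis. Some judgement remains, for example whether symptoms occur only during intoxication.
- **Certainty.** A reader might infer that upcoming assignments are known in advance. That would require knowing the block size, and nothing says that the team knows it or that it is fixed. Its absence from an article is normal and is no fault.
- **Cause.** A reader might blame small strata. The sensitivity check shows similar rates in 8 strata and in 28, and the article does not say that each service is a separate level.
- **Motive.** A reader might assume that the coordinator is close to the intervention team. The article does not say so. Moderation is led by a different role, the trial moderation coordinator.
- **Detectability.** Social functioning and many other measures are taken before randomisation, so an imbalance in them could be seen. The repeated-measures model also includes baseline as a time point. Unmeasured differences in prognosis would escape both.

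None of this separates the two duties. Hiding the schedule does not answer the point, because the inference uses past results and not the list.

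**Conclusion.** The weakness is real and arises from what the article states: one role advises on entry and knows every earlier allocation under 1:1 permuted blocks. A guess made from that knowledge is right about 65% to 75% of the time for assumed block sizes of 2 to 6, and somewhat less often once the gap of up to a month is allowed for, against 50% without it.

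This is weakened concealment and not demonstrated bias. The documents do not support the inference that selection took place. Its size, if any, is unknown: assumed shifts of 0.05 to 0.2 SD give a bias of about 0.02 to 0.09 SD and a one-sided error of about 3% to 9% instead of 2.5%, before any baseline adjustment. The upper end requires the shift to apply across all enrolled participants, which is more than an occasional borderline decision would produce.

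**What to change.** Separate the two duties in either of these ways:

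- have eligibility confirmed in consultation with an existing team member who receives no allocation notices; or
- have the RPMS send the allocation message to participants automatically, and remove whoever advises on eligibility from the notification email.

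In either case, state in the protocol that no one who advises on eligibility may see earlier allocations. The automatic message is preferable to handing notification to the moderation lead, which would create a new contact between the intervention team and participants allocated to treatment as usual. Varying the block size would not be enough: mixed blocks of 4 and 6 still leave about 67%.

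The cost is a reassignment of duties, a change to the RPMS notifications and a protocol wording change. Sample size and analysis are unaffected.

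For participants already randomised, disclose the overlap of roles in the trial report and inspect baseline balance between the arms.
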